**Methods:**

This 1:1 randomised controlled trial will enrol 260 participants with subthreshold depression randomizing into 2 groups (online exercise intervention versus usual care control). The intervention consists of twice-weekly 1-h exercise online classes over 12 weeks, which will be led by certified instructors. Data will be collected at baseline (T0), immediate post intervention (T1), 3-month post intervention (T2) and 9-month post intervention (T3). The primary outcome is depressive symptoms measured by the Chinese version of Beck Depression Inventory-II (BDI-II) at T1. Secondary outcomes include anxiety symptoms, quality of life, physical activity levels, feasibility and acceptability, medication use and health service utilization, and cost assessment. Intention-to-treat analysis will be performed.

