### Objectives and Hypotheses

The primary objective of the study is:

To examine the efficacy of a 12-week online instructor-led exercise intervention (EIM) when compared to usual care control in reducing depressive symptoms among people with subthreshold depression in primary care.

The secondary objectives of the study are:To examine the efficacy of a 12-week online instructor-led exercise intervention (EIM) when compared to usual care control in reducing anxiety symptoms and improving quality of life among people with subthreshold depression in primary care; andTo examine the cost-effectiveness of the intervention.

The hypotheses of the study are:The online instructor-led exercise intervention will be more effective when compared to usual care in reducing depressive symptoms among patients with subthreshold depression (primary hypothesis);The online instructor-led exercise intervention will be more effective in reducing anxiety symptoms and improving quality of life when compared to usual care (secondary hypothesis); andThe online instructor-led exercise intervention will be a cost-effective intervention in primary care (secondary hypothesis).

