### Sample size

From a previous trial on assessing the efficacy of group-based behavioural activation with mindfulness for treating subthreshold depression in primary care in Hong Kong, mean (standard deviation) of BDI-II score at baseline for intervention and usual group were 19.18 (8.35) and 17.68 (9.52) respectively among participants with subthreshold depression. Pooled mean and standard deviation were 18.43 and 8.95 from two groups. For moderate baseline severity, the minimum clinically important difference (MCID) on the BDI-II was estimated at 3.5 points [24]. Assuming at least the MCID could be seen in the online exercise programme at 4-month post randomisation compared to usual care, sample size of 104 each group achieve 80% power to detect the difference of 3.5 points in BDI-II with a common standard deviation of 8.95 at a significance level of 0.05 using two-sided t-test. The corresponding effect size of 0.39 is similar to the finding from a systematic review that physical activity is beneficial for improving depressive symptoms with effect size of 0.43 [8]. From our experience in running online exercise intervention for people with subthreshold depression, a dropout rate of 13% at 12 month follow up was observed. To be conservative, we assume drop out to be 20%, and set our enrolment target at participants in total of 260 with 130 participants in each group.

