### Statistical analysis

Baseline characteristics of the two groups will be compared using chi-square test for categorical variables and independent samples t-test for continuous variables. Analysis of covariance (ANCOVA) for the BDI-II score at T1 will be conducted as the primary analysis, with the BDI-II score at T0 and other characteristics with significant between-group difference at T0 as covariates in the model for sensitivity analyses. Effect size estimates will be obtained for the primary outcome, with the between group effect sizes (Cohen’s d) being calculated using the mean differences from baseline and the SDs of the two groups at each time point. For the secondary analysis, linear mixed models (LMM) with random intercept will be applied to investigate the significant changes over time, for both primary and secondary outcome measures. The LMM approach is in line with the intention-to-treat principle, to include all subjects for the analysis and use all available data to assess the treatment effect over time. Maximum likelihood estimation (MLE) will be employed to handle missing data in the analyses with LMMs. A sensitivity analysis will be conducted using imputed data generated by multiple imputation. Furthermore, compliance with prescribed exercises will be added into the models to explore if this is predictor of changes in health outcomes.

In the cost-utility analysis, utility will be measured with quality adjusted life years (QALYs) based on SF-12 using the Hong Kong weights. The area under curve approach will be used to calculate the utilities at follow-ups after adjusting for baseline utility. In the cost-effectiveness analysis, remission of depressive symptoms (BDI-II score of < 14) will be used as outcome. Using both provider and societal perspectives, incremental cost-effectiveness ratio (ICER) will be calculated by dividing cost difference of two groups by between-group effect difference. We will use bootstrapping technique to assess the uncertainty of the ICER estimate. Due to the lack of a local willingness-to-pay threshold, we will generate cost-effectiveness acceptability curves to evaluate the probability of cost-effectiveness of the proposed intervention.

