The significant level will be set as 0.05 for the statistical tests. To address the issue of multiple testing in our exploratory secondary analyses, we will employ the Bonferroni correction to control the overall type I error rate by adjusting the significance threshold for each individual test. This adjustment ensures a rigorous control of false positive results while allowing for the exploration of associations between the online exercise intervention and secondary outcomes.

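### Single-step Bonferroni for the secondary tests is valid but needlessly conservative; Holm's step-down gives the same family-wise control and never rejects less

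*Protocol article*

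**What the plan says.** The last paragraph of Statistical analysis in the protocol article sets the level: "The significant level will be set as 0.05 for the statistical tests". It then addresses multiplicity for analyses that it calls exploratory: "we will employ the Bonferroni correction to control the overall type I error rate", and says this is done by changing the threshold of each test separately. One adjusted threshold per test, with no ordering of p-values, is single-step Bonferroni.

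Objectives and Hypotheses states a directional hypothesis for two of the secondary outcomes: the intervention "will be more effective in reducing anxiety symptoms and improving quality of life when compared to usual care (secondary hypothesis"). The Abstract lists the secondary outcomes more widely: "Secondary outcomes include anxiety symptoms, quality of life, physical activity levels, feasibility and acceptability, medication use and health service utilization, and cost assessment". Statistical analysis says of the secondary analysis that "linear mixed models (LMM) with random intercept will be applied to investigate the significant changes over time, for both primary and secondary outcome measures".

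The article does not give the number of tests in the corrected family, or any power figure for a secondary outcome.

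**The concern.** Bonferroni compares every p-value with 0.05/m. Holm compares the smallest with 0.05/m and relaxes the threshold after each rejection. The error guarantee is the same, and Holm can only add rejections.

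Holm gains most when several effects in the family are real. The trial's own secondary hypothesis predicts this for anxiety and quality of life. At stake is some power on secondary outcomes that the plan could keep without more participants or data.

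**Working it through.** **1. The plan's own figure.** The only design calculation is for BDI-II at T1: difference 3.5, SD 8.95, 80% power, "at a significance level of 0.05 using two-sided t-test".
- Effect size: 3.5/8.95 = 0.391.
- Normal approximation: n = 2 × (1.960 + 0.842)² × 8.95²/3.5² ≈ 103 per group. The exact t-test gives 103.6, hence 104, with power 0.801.
- Dropout: 104/(1 − 0.20) = 130 per group, 260 in total.

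The stated sample size reproduces, and nothing below changes it.

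**2. Does Bonferroni deliver what is claimed?** For m independent tests the family-wise error is 1 − (1 − 0.05/m)^m.
- m = 3: 4.92%; m = 4: 4.91%; m = 12: 4.89%.
- Unadjusted, 1 − 0.95^m gives 14.3%, 18.5% and 46.0%.

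It does.

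**3. Why Holm has the same guarantee.** Order the p-values and compare the i-th smallest with 0.05/(m − i + 1), stopping at the first failure. For m = 3 the thresholds are 0.0167, 0.025 and 0.05, against 0.0167 throughout for Bonferroni. Suppose m₀ null hypotheses are true. The first false rejection comes at step m − m₀ + 1 at the latest, so it needs a true-null p-value of at most 0.05/m₀. The probability of that is at most m₀ × 0.05/m₀ = 0.05 under any dependence. No Holm threshold is below 0.05/m, so every Bonferroni rejection is also a Holm rejection. The first threshold is the same in both, so the chance of at least one rejection is identical.

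**4. Size of the gain.** The inputs are:
- From Sample size: 104 completers per arm and d = 0.39. This d is the BDI-II design effect, borrowed here for the secondary outcomes.
- Assumed: d = 0.25 as an alternative; correlation between tests 0 or 0.5; m = 3 (BAI and two SF-12 summaries), 4 (adding IPAQ-SF) or 12 (four scores at three follow-up visits).

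Bonferroni power can be checked by hand. The expected z is 0.39 × √(104/2) = 2.812.
- m = 3: critical value 2.394, power = Φ(2.812 − 2.394) = Φ(0.418) ≈ 66%.
- m = 12: critical value 2.865, power = Φ(2.812 − 2.865) = Φ(−0.053) ≈ 48%.

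Exact t-test values are slightly lower, 65.5% and 46.8%. Holm was simulated with 200,000 replicates. Results at correlation 0.5:

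| m | Real effects | d | Average power per real effect, Bonferroni | Holm | Gain (points) |
|---|---|---|---|---|---|
| 3 | 3 | 0.39 | 66% | 74% | 7.7 |
| 3 | 1 | 0.39 | 66% | 66% | 0.1 |
| 3 | 3 | 0.25 | 28% | 32% | 4.7 |
| 4 | 4 | 0.39 | 62% | 71% | 9.0 |
| 4 | 2 | 0.39 | 62% | 65% | 2.2 |
| 12 | 12 | 0.39 | 48% | 59% | 10.9 |
| 12 | 6 | 0.39 | 48% | 51% | 3.2 |
| 12 | 12 | 0.25 | 14% | 18% | 3.3 |

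Independent tests give a similar picture, with gains from 0.2 to 10.7 points. With all effects real at d = 0.39 and correlation 0.5, the chance of detecting every one rises from 42% to 60% for m = 3 and from 7% to 30% for m = 12. The chance of detecting at least one is 87.7% (m = 3) and 91.3% (m = 12) under either method.

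**5. Error check.** With no real effects, both methods gave the same family-wise error: 4.9% to 5.0% at correlation 0 and 3.9% to 4.4% at correlation 0.5. With some effects real, Holm's highest value was 4.4%. No replicate had a Bonferroni rejection that Holm missed.

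**The case against.** The strongest reply is that nothing here is wrong. Bonferroni is valid, gives the control the article claims, and contradicts no other statement. The article does not claim maximum power. It labels these analyses exploratory ("To address the issue of multiple testing in our exploratory secondary analyses"), and any inaccuracy is on the conservative side. All of this stands and limits the point to an efficiency suggestion.

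The reply on size also stands. The 11-point gain needs all 12 effects to be real at the primary outcome's effect size. The count of 12 is an assumption, because the article specifies mixed models over time and not a t-test per score and visit. With few real effects the gain all but vanishes.

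Nor is the change entirely free. Bonferroni has simple matching simultaneous intervals and lets each test be judged alone. Holm needs all p-values of the family together and has no equally simple intervals.

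A reader might go further and infer that anxiety and quality of life share one divisor with every other secondary test, so the family should be cut to BAI and SF-12 at T1 with the rest left unadjusted. The article does not support this. It defines no family, and a condensed article commonly leaves that to the analysis plan. Its secondary hypothesis is not restricted to T1. Cutting the family would also remove protection that the present wording gives to other secondary results. On the figures above, going from 12 tests to 3 already lifts Bonferroni power from 48% to 66%. That 18-point gain comes from giving up correction elsewhere, so it is a trade-off and not part of this point.

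**Conclusion.** The point holds as an optional improvement. Single-step Bonferroni is a sound choice that a method with the same error guarantee equals or beats in rejections. That ordering needs no assumption about family size or dependence.

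The size of the benefit does rest on assumptions: between about 0 and 11 points of average power per test, depending on how many effects are real, how large they are and how many tests are corrected. It would be wrong to conclude that the plan contains an error, or that real secondary effects will generally be missed because of Bonferroni. The primary ANCOVA of BDI-II at T1 and the sample size are untouched.

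**What to change.** In the last paragraph of Statistical analysis, replace the Bonferroni correction with the Holm step-down (Bonferroni–Holm) procedure at a family-wise level of 0.05. Apply it to whatever family of secondary tests the plan already corrects, and leave that family unchanged.

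This costs one sentence and needs no data or participants. It should be made before any outcome results by arm are seen, because a later switch would look driven by the data. The plan should also say which confidence intervals will accompany the Holm decisions. If Bonferroni intervals are kept, some may include no difference where Holm rejects, and the report should say so.

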### Ethical concerns and data monitoring

Participants will be informed of the details about this study, including the objectives, procedures, randomization arrangement, and schedule of intervention and data collection. Research staff will allow ample time for the potential participants to decide whether they opt to join the study or not. Written consent will be obtained from all participants. Participants can choose to withdraw from the study at any time. In case of any adverse event, the ethics committee will be notified immediately. Moreover, all participants will be covered by clinical trial insurance. Qualified physical trainers with adequate knowledge and experience to assess participants’ physical health and fitness levels will be hired to lead the intervention. They will help identify any potential risks to ensure the exercise activities are performed safely.

In addition, a data and safety monitoring committee will be established consisting of a biostatistician being the chair of the committee, one expert in mental health and one expert in public health to monitor the study outcomes on a regular basis to ensure there is no safety issues arise from the study. All committee members will be independent from the study. The committee can decide to stop the trial if there are strong evidence of safety issue caused by intervention. To ensure subject privacy and research data confidentiality, all hardcopies of the questionnaires and data collected will be locked in cabinets, and their electronic versions will be stored in password protected computers.

## Discussion

Numerous studies have confirmed the benefits of exercise in reducing depressive symptoms among people with diagnosed depression, but only limited studies [25] were conducted in primary care. Moreover, most have short follow-ups and few explored the effectiveness of exercise intervention among patients with subthreshold depression and examined the prevention of having clinically relevant depressive symptoms or major depression [8]. In addition, as the COVID pandemic has prompted the rapid development and adoption of Zoom conducted exercise programme and there are limited studies using online exercise intervention for depressive symptoms [26], this also provides a unique opportunity to examine the efficacy of Zoom exercise programme.

A study in Sweden [19] showed that physical exercise intervention was a cost-effective treatment for mild to moderate depression in primary care setting compared to treatment as usual, with an incremental cost per quality-adjusted life-year (QALY) gain of 14,571 euros. However, the same study also found that internet-based cognitive behavioural therapy (ICBT) resulted in a lower incremental cost per QALY gain of 8,817 euros. One of the possible reasons for the discrepancy is that the physical exercise intervention required face-to-face sessions, which resulted in transportation cost and cost of securing venues for the sessions. In contrast, such costs were not incurred in the ICBT arm. If the physical exercise intervention were converted to an online format, the cost-effectiveness might be improved.

Therefore, we propose to examine the efficacy and cost-effectiveness of a complex intervention (EIM) using Zoom supported by other components in reducing depressive symptoms among patients with subthreshold depression in primary care. Future effectiveness study can be conducted to determine whether the intervention produces the proven efficacy in real-world setting.

## Publication and data availability

The results of this study will be published in peer-reviewed journals and presented in public conferences, in accordance to the CONSORT-2010 standards. The datasets generated and/or analysed during the study will be available from the corresponding author upon reasonable request following the completion of all primary publications derived from these datasets.

## Data Availability

No datasets were generated or analysed during the current study.

## Abbreviations

ANCOVA: Analysis of covariance
BAI: Beck Anxiety Inventory
BDI-II: Beck Depression Inventory-II
CBT: Cognitive behavioural therapy
EIM: “Exercise Is Medicine” programme
FMC: Family Medicine Centre
GOPC: General Outpatient Clinic
ICER: Incremental cost-effectiveness ratio
IPAQ-SF: International Physical Activity Questionnaire – Short Form
LMM: Linear mixed model
MCID: Minimum clinically important difference
MLE: Maximum likelihood estimation
NTEC: New Territories East Cluster, Hospital Authority, Hong Kong
PHQ-9: Patient Health Questionnaire-9
QALY: Quality adjusted life year
SF-12: Medical Outcomes Study Short-Form Health Survey
